### Plans to promote participant retention and complete follow-up {18b}

Trial retention will be actively monitored at the site by the project coordinator and data lead. If participants do not attend a scheduled session or outcome assessment, a maximum of three follow-up attempts will be made by the team using both in-person and telephone methods. Contact details will be recorded for each participant including home address, a personal telephone number, as well as home addresses and telephone numbers of friends, family members, and community leaders who may be contacted (specific consent will be asked for this).

### Data management {19}

Trial data will be captured using the secure ODK server hosted by the London School of Hygiene and Tropical Medicine. Data will be collected using password-protected tablets at screening, baseline, 3 and 12-month follow-ups. A participant ID will be generated through ODK, and this ID will be used throughout the trial. The identifying key will be kept securely and separate from the rest of the data on a separate password-protected Sharepoint site that is only accessible to those who are unmasked. Data collection tablets are password protected, and data that is uploaded through ODK will be encrypted. To prevent data loss, copies of the data will be saved weekly on two password-protected external hard drives, one in Kampala and one in Arua. Standard operating procedures are in place to guide data entry, monitoring, and management, as well as a data management plan.

Data transfer procedures will be in place between the research partners to ensure anonymity, encryption, and secure storage compliance. Data will be transferred using password-protected Sharepoint. After analyses are complete (> 2 years after unmasking), data will also be made available for download in the London School of Hygiene and Tropical Medicine open data repository.

Qualitative data will be audio recorded, and transcribed. Audio recordings will be deleted from the recorders as soon as the transcription is complete. Furthermore, all identifying information will be removed from the transcripts. For both qualitative and quantitative data, no attributable data will be used in publications or presentations.

### Confidentiality {27}

The confidentiality of participants will be protected using the encrypted ODK server and unique participant ID number to identify each participant. All the members of the research and implementation team will be trained on maintaining the confidentiality of participants, including ensuring privacy when conducting interviews and assessments. Data management and security will abide by the requirements of the General Data Protection Regulations (GDPR) and any subsequent amendments.

### Plans for collection, laboratory evaluation and storage of biological specimens for genetic or molecular analysis in this trial/future use {33}

This trial does not involve collecting biological specimens for storage or evaluation.

## Statistical methods

### Statistical methods for primary and secondary outcomes {20a}

The statistical analysis plan will be finalised and approved by the Data Safety and Management Board (DSMB) prior to unmasking of the trial and analysis. Quantitative analyses will be conducted using Stata 17.0 statistical software. Initial analyses will compare baseline characteristics of study participants by arm using a descriptive analysis. If substantial baseline imbalances exist in characteristics that are likely to affect outcomes, these will be adjusted a priori in outcome analyses. The initial analysis will compare participants who did and did not consent to participate in the intervention following initial screening.

Binary outcomes will be analysed using logistic regression or negative binomial regression, depending on the distribution. Marginal standardisation and delta methods [52] will be used to calculate adjusted risk ratios if logistic regression is used. Continuous outcomes will be analysed using linear regression, after transformation if needed, and adjusted mean differences reported. Data from 3- and 12-month follow-up points will be analysed and interpreted separately.

All models will be adjusted for village using a random effect to account for village-level stratification of randomisation. Models will also be adjusted for baseline characteristics that differ substantially across arms as identified in descriptive analyses, and baseline measures of the outcome variable. Village-adjusted and fully adjusted (if appropriate) model results will be presented. All findings will be reported using CONSORT guidance [53] and intention-to-treat (ITT) principles will be used for the primary analysis of findings.

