**Secondary outcomes**			
Percentage of days abstinent	TLFB [28]		X
Alcohol misuse	• Alcohol Use Disorders Identification Test (AUDIT) [23] • Alcohol, Smoking and Substance Involvement Screening Test (ASSIST) [29]	X	X
Psychological distress	Kessler-10 (K10) [24]	X	X
Depression	Patient Health Questionnaire-9 (PHQ-9) [30]	X	X
Anxiety	Hopkins Symptom Checklist Anxiety (HSCL-A) [31]	X	X
Symptoms of PTSD	PTSD Checklist for DSM-5 (PCL-6) [32]	X	X
Functional disability	WHO Disability Assessment Schedule (WHODAS 2.0) [33]	X	X
Perpetration of intimate partner violence	United Nations Multi-Country Study on Men and Violence [34]	X	X
Health economic indicators	• EuroQol-5D-5L (EQ-5D-5L) [35] • Subjective wellbeing [36, 27] • Oxford Capabilities Mental Health questionnaire (OxCAP-MH) [37] • User cost questionnaire	X	X

**Table 2 Tab2:** Details on CHANGE intervention trial outcome measures

Instrument	Description	Outcome	Contextual validity
Timeline follow-back [28]	Diary method to retrospectively assess daily estimates of drinking	Percentage days abstinent (PDA): Proportion of past 14 days on which participant was abstinent; analysis based on distribution	Validated for alcohol use assessment including in Uganda [28, 38, 39]
AUDIT [23]	Ten-item questionnaire to measure alcohol intake, identify potential dependence on alcohol; and experiences of alcohol-related harm. Each item is assessed on a scale of 0 to 4	Mean score and dichotomous as a secondary outcome	Validated with South Sudanese populations [40], and in Rhino settlement (https://www.elrha.org/project/improving-the-mental-health-of-refugee-men-through-guided-self-help-a-scalable-intervention-for-a-critical-link-in-humanitarian-programming/, Paper forthcoming)
ASSIST [29]	Eight-item screening questionnaire on estimates of alcohol use, tobacco products, and other drugs across the lifetime and in the past 3 months. Measured on a scale of 0 to 7	Mean score	Validated in a multisite international study covering Australia, Brazil, India, Thailand, UK, USA, and Zimbabwe [29]. It has also previously been validated in Rhino settlement (https://www.elrha.org/project/improving-the-mental-health-of-refugee-men-through-guided-self-help-a-scalable-intervention-for-a-critical-link-in-humanitarian-programming/, Paper forthcoming)

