### Sample size {14}

A sample size of 500 enrolled participants (250 in each arm with 1:1 allocation) will provide 90% power to detect a difference in the PDA from alcohol of 55% in the EUC arm vs 68% in the CHANGE arm (SD = 37%) at 3 months follow-up with alpha = 0.05. The sample size calculation accounts for 20% loss to follow-up at 3 months. The estimated PDA and SD are conservative, based on the CAP trial (54% vs 69%) (Nadkarni et al., 2017).

For the semi-structured interviews, all facilitators (*N* = 17), supervisors (*N* = 4), and outcome assessors (*N* = 11) will be invited to participate, plus 20 family members of intervention completers, 20 intervention completers, 20 participants in the control group, and as many participants who dropped out as possible until saturation is reached. A purposive sampling procedure will be used when selecting these participants to ensure maximum variation.

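### The adjustment covariates are chosen from observed differences between arms, a choice called a priori that no pre-unmasking SAP can fix, and neither of the two planned models is named as primary

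*Protocol article*

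**What the plan says.** All of this is in the protocol article, mainly under Statistical methods for primary and secondary outcomes {20a}.

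- **Covariates, sentence on baseline imbalance.** If substantial imbalances are found in characteristics thought likely to influence outcomes, "these will be adjusted a priori in outcome analyses".
- **Covariates, sentence on the outcome models.** "Models will also be adjusted for baseline characteristics that differ substantially across arms as identified in descriptive analyses". The same sentence adds the baseline measure of the outcome. The restriction to outcome-related characteristics does not appear here. Neither sentence gives a threshold or a candidate list.
- **Models reported.** "Village-adjusted and fully adjusted (if appropriate) model results will be presented". A village random effect is in every model. Neither model is called primary.
- **Scale.** "Continuous outcomes will be analysed using linear regression, after transformation if needed, and adjusted mean differences reported". For the primary outcome, Table 2 says: "Proportion of past 14 days on which participant was abstinent; analysis based on distribution".
- **Sizing.** The Sample size section {14} uses "55% in the EUC arm vs 68% in the CHANGE arm (SD = 37%) at 3 months follow-up with alpha = 0.05", a difference in percentage points.
- **Safeguard.** The SAP is to be finalised, with DSMB approval, before unmasking and analysis. Section {17a} lists the trial statisticians as masked.

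**The concern.** A covariate set triggered by an observed difference between arms is known only once baseline data are open by arm. It is therefore not a priori, and the SAP safeguard cannot reach it while the rule stands. In a properly randomised trial such differences are chance, so their size says nothing about whether a covariate predicts the outcome. The model's usual standard error also takes no account of covariates having been selected this way.

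With two models planned and no lead, the headline estimate and p-value are not uniquely defined. A reader cannot tell whether the village-adjusted model already contains baseline PDA, which decides how far apart the two results can lie. A result on a transformed scale would not be the percentage-point difference on which the trial was sized.

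**Working it through.** **1. The plan's own figure.** Inputs from section {14}: 500 enrolled, 20% loss, so 200 per arm analysed; difference 68 − 55 = 13 points; SD 37; alpha 0.05, taken as two-sided.

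- Standard error = 37 × √(2/200) = 3.7 points.
- Power ≈ Φ(13/3.7 − 1.96) = Φ(1.55) ≈ 94%.
- For 90% power, 171 analysed per arm suffice: 171/0.8 = 214 enrolled per arm, 428 in all.

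The stated 90% is not reproduced, but the gap is on the safe side and does not bear on this point. The standardised planned effect is 13/37 = 0.35 SD.

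**2. How much the undefined threshold decides.** For a standardised covariate, the chance difference between arms has standard error √(2/n). Assume eight independent candidate covariates.

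| n per arm | Standard error | At least one above 0.1 SD | At least one above 0.2 SD |
|---|---|---|---|
| 250 (randomised) | 0.089 | 1 − (1 − 0.264)^8 = 91% | 1 − (1 − 0.0253)^8 = 19% |
| 200 (analysed) | 0.100 | 1 − (1 − 0.317)^8 = 95% | 1 − (1 − 0.0455)^8 = 31% |

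The reading given to *substantially* therefore largely settles which model is fitted.

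**3. Null rejection rate.** Simulation of 6,000 null trials per column, 200 per arm, with a 14-day U-shaped outcome of mean 55 and SD 37. It has one baseline outcome measure and eight candidate covariates, three of them prognostic. Covariate strength and thresholds are assumptions, and the village effect is omitted.

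| Analysis, nominal 5% | Weaker covariates, cut-off 0.1 SD | Stronger, 0.1 SD | Stronger, 0.2 SD |
|---|---|---|---|
| Baseline outcome plus all eight, fixed | 5.1% | 5.1% | 4.8% |
| Baseline outcome plus imbalanced covariates | 4.8% | 3.7% | 4.2% |
| Better of the two models, baseline outcome only in the second | 6.9% | 6.8% | 6.4% |
| Better of the two models, baseline outcome in both | 6.0% | 6.2% | 5.3% |

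A second set of assumptions uses baseline PDA with r = 0.4 and ten further covariates, four with r = 0.2. It gives 4.0 to 4.6% for the imbalance rule, against about 5% for a fixed list. The standard error is roughly 2 to 6% too wide, and the better of the two models rejects 6.5 to 6.8%.

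The direction has a simple cause. A prognostic covariate that happens to be balanced is left out, so its variance stays in the residual and in the standard error, although it adds little error to the estimate in that trial.

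**4. Effect on the estimate.** In the step 3 simulation, the unadjusted and imbalance-adjusted estimates differ by a median of 0.9 to 1.4 points and a 95th percentile of 3.1 to 4.0 points, against a target of 13. They disagree on significance in 3.6 to 4.7% of null trials.

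**5. Power at the planned effect.** At 0.35 SD under the second set of assumptions, the imbalance rule has 97.9%. A fixed model with baseline PDA and two further covariates, each given r = 0.2, has 98.2%. The difference is 0.3 points.

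**The case against.** The strongest defence is that the SAP comes before unmasking and is not shown. Naming the lead model is ordinary SAP content, and a transformation could be chosen on pooled, masked data with little harm to the error rate. This stands for scale and lead model. A reader might infer that the whole primary analysis is settled after the results are seen, and the protocol does not support that. The defence fails for the covariate rule. An SAP could add a threshold and a candidate list, making the choice mechanical, but the set would still depend on arm-level data and the standard error would still be off.

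Other tempting readings also go too far:

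- **That the covariate rule inflates type I error.** Alone it is nominal to mildly conservative. The 6.5 to 7% arises only if the analyst leads with the better result, whereas the protocol plans to present both models.
- **That the rule ignores prognosis.** One of the two wordings limits adjustment to characteristics likely to affect outcomes. The defect is that the other drops the limit.
- **That the village-adjusted model omits baseline PDA.** The text can be read either way.
- **That the trial loses material power.** At the planned effect it does not.
- **That a non-normal outcome rules out linear regression.** With about 400 men analysed, a comparison of means remains reasonable. The issue with transforming is the change of scale.

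**Conclusion.** The point holds in a limited form. The covariate rule contradicts its own a priori label, cannot be pre-specified as written, and comes in two wordings that differ. The absence of a named lead model and the unclear place of baseline PDA add to this, though the SAP could settle both.

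The consequences are modest: about 4 to 4.6% null rejection for the rule alone (3.7 to 4.8% over all scenarios tried), at most about 6.5 to 7% with free choice of lead model, and under about 1 point of power at the planned difference. These sizes rest on assumed numbers and strengths of covariates, assumed imbalance thresholds, and simulations without a village effect; the protocol gives none of these inputs. The contradiction in the text rests on no assumption. The trial remains valid, but its headline result should be uniquely defined, so the change should be made.

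**What to change.** In section {20a} and the SAP, before unmasking:

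1. Delete the two sentences that make adjustment depend on observed imbalance, keeping adjustment for the baseline measure of the outcome.
2. Name one primary model for 3-month PDA: linear regression with the village random effect, baseline PDA and a short fixed list of prognostic baseline measures, all included whatever the observed balance. AUDIT and K10 are examples. The protocol does not show that they predict PDA, and eligibility restricts their range, so the trial team should confirm the list on subject-matter grounds.
3. State that the primary effect is a difference in percentage points on the untransformed scale, matching the 55% versus 68% used for sizing, and amend the Table 2 entry for PDA accordingly.
4. Label the village-only model, and any transformed analysis, as sensitivity analyses.

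The cost is wording in the protocol and SAP. AUDIT and K10 are used at screening, and section {18a} has primary and secondary outcome data collected at baseline, so no new data are needed and the sample size is unchanged.

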### Interim analyses {21b}

No interim analysis will be conducted. The DSMB will receive access to the unmasked data during the trial, and they will be responsible for reviewing the data and making any decisions related to the termination of the trial.

### Methods for additional analyses {20b}

For the cost-effectiveness analysis, the costs, disability-adjusted life years (DALY) averted, and quality-adjusted life years (QALY) gained will be estimated for each participant. Incremental cost-effectiveness ratios will be estimated, and uncertainty will be represented by producing a cost-effectiveness plane and cost-effectiveness acceptability curve. Furthermore, a deterministic sensitivity analysis around assumptions made on the duration of effect and discount rates will be carried out. Cost-effectiveness will be evaluated against a pre-determined threshold and compared to similar programmes addressing alcohol misuse and mental health in the region and elsewhere. Reporting of the economic evaluation will follow the recently published Consolidated Health Economic Evaluation Reporting Standards 2022 [54].

Qualitative data will be transcribed and translated into English from the language the interview was conducted in. Data will be analysed thematically using a prescheduled theoretical framework codebook drawing on Normalization Process Theory (NPT) [55] in NVivo © QSR International. The themes that come from the analysis will be mapped onto the twelve NPT constructs described in the NPT codebook [55]. The codebook will be used as a guide for interpretation of the data, rather than a scriptural authority, as recommended by May et al. [55]. Furthermore, codes, themes, and mapping onto NPT domains will be peer-reviewed in regular meetings with the wider research team to ensure the reliability of findings.

### Methods in analysis to handle protocol non-adherence and any statistical methods to handle missing data {20c}

Outcome and covariate data will be investigated for missingness, and if the missingness proportion is high (> 10%) multiple imputation methods will be considered. The outcomes will be reported using consolidated standards of reporting trials (CONSORT) guidance [56] and intention-to-treat (ITT) principles will be used for the primary analysis of findings.

### Plans to give access to the full protocol, participant-level data and statistical code {31c}

Two years after unmasking and completion of analyses, data will be stored in a publicly available repository, London School of Hygiene and Tropical Medicine Data Compass (https://datacompass.lshtm.ac.uk). The data stored will be anonymised participant data that excludes information classed as internal, confidential, or highly confidential.

## Oversight and monitoring

### Composition of the coordinating centre and trial steering committee {5d}

The current trial will be supported by a Trial Steering Committee (TSC) and a Trial Management Committee (TMC). The role of the TSC is to provide overall governance and oversight of the study and the definite RCT and ensure that it is being conducted in accordance with the protocol and the relevant regulations. The TSC provides advice to the TMC on all aspects of the trial. The TSC will meet every 6 months. Members of the TSC are experts from Uganda as well as international experts in alcohol misuse, mental health and psychosocial support, mental health in humanitarian settings and epidemiologists with expertise in conducting trials in complex settings.

The remit of the TMC is to provide country-specific advice. The members of the TMC are composed of the overall PI (DF), and the site PIs (WT and EK). The TMC will report to the DSMB and funder on the progress of the Trial.

### Composition of the data monitoring committee, its role and reporting structure {21a}

The DSMB members are independent from the trial team. The role of the DSMB is to monitor the data emerging from the RCT, as it relates to the safety of participants, and to advise the TSC on whether there are any reasons for the trials not to continue. It is the only body involved in CHANGE that has access to the unmasked comparative data during the trial. The DSMB will meet twice a year, and it will be responsible for (i) determining whether an interim analysis should be undertaken, (ii) any additional safety issues for the CHANGE project that need to be considered, (iii) report to the TSC and to recommend on the continuation of the trial, and (iii) consider any requests for release trial data and to recommend to the TSC on the advisability of this.

### Adverse event reporting and harms {22}

An overview of types of expected and unexpected SAEs and AEs in the current trial can be found in Table 3. SAEs and AEs that are reported by the participant or observed by the outcome assessors or the intervention facilitators, during any of the outcome assessment or intervention sessions will be notified to the local project coordinator and site PIs, who will be unmasked for that individual if the SAE/AE is intervention related.

**Table 3 Tab3:** Expected and unexpected SAE and AEs

	Expected	Unexpected
SAE	Victimisation (violence against the trial participant or nuclear family)	Death of the trial participant due to suicide
	IPV (violence against family members by participant, or violence against participant by family member)	Death of the trial participant due to other causes
	Suicide attempt	Hospital admission of trial participant due to a psychiatric problem
	Stigmatisation	Hospital admission of trial participant due to other causes
	Serious lack of food	
AE	Clinical deterioration of the participant	
	Emotional distress caused by a trial procedure (either by the outcome assessment or the intervention delivery)	

A critical incident register will be maintained during the study to record any such events, and a specific report will be completed by the local project coordinator for each individual event. Based on the type of event, the participant will be asked to give consent for further evaluation, assessment, and/or follow-up by a designated health professional (e.g. psychologist (for stigmatisation and victimisation), PCO, or clinical officer (for all other SAEs, e.g. medical emergencies). If the participant was in the intervention arm of the trial, once they are referred to specialist care, they will not be able to re-enter the trial at a later stage. The exception to this is referrals for intimate partner violence, as participants who are referred to support services will not be excluded from the trial. Instead, they will be encouraged to access protection services and will be offered a follow-up with a social worker via the phone. Referrals for intimate partner violence will be made by an outcome assessor where the participant discloses potential intimate partner violence on the UN multi-country measure of violence during outcome assessment, or if they disclose intimate partner violence during a session with a facilitator.

Completed SAE/ AE reports, e.g. assessment by the nominated health professional will be sent to the project coordinator, who will in turn forward the same report without the participants’ ID to the site PI’s. The site PIs will compile these reports and forward to the overall PI when the reports are received. If the SAE is classified as needing immediate reporting, the site PIs will forward this report to the DSMB and the London School of Hygiene and Tropical Medicine Ethics Research Committee and/or the local IRB MildMay Uganda Research Ethics Committee (MUREC) within 3 working days of detection.

The response to SAEs related to stigmatisation will follow the same general SAE response as noted above but will also always include an evaluation by an independent PCO to ensure the quality and correct identification of these types of SAEs. For events determined by the independent clinician to be SAEs, the project coordinator will then forward the SAE for further referral to the appropriate professional. The time from initial detection of a potential SAE by the implementation team, to the project coordinator sending the SAE/AE report to the nominated healthy professional is two working days. Following these 2 days, if it classifies as an SAE, the report will be submitted to the DSMB, London School of Hygiene and Tropical Medicine ethics committee and MUREC. All SAEs and AEs will be followed up until they have abated, or until a stable situation has been reached.

